### **Appendix 3\_Study protocol EEBK.ЕП.2022.32**

#### **Protocol of study “The investigation of the effects of different types of exercise in neuroplasticity and in clinical condition, in people with Multiple Sclerosis”.**

Multiple sclerosis (MS) is the most common inflammatory, demyelinating and neurodegenerative disease of the central nervous system (CNS) (1). The prevalence of MS during the last two decades, has significantly increased all over the world (2,3), with predominance among young people (4). The low mean age of diagnosis (i.e., 32 years old), along with an average of seven years' shorter life expectancy (i.e., 74.7 years) compared to the general population (5–7), highlights the need for a lengthy support, resulting in increased financial and social burden (4). Furthermore, both MS patients and their caregivers, are facing several psychological and social difficulties due to social isolation, poorer quality of life (QoL) (8,9).

Relapsing-remitting (RR) MS is a type of MS (10) which is characterized by periods of relapses followed by partial or complete recovery (1). However, a great amount of patients diagnosed with RRMS transit to secondary-progressive MS (SPMS) within 10 years, whereas some others transit within 25 years (1). Individual clinical condition varies between pwMS and symptoms are diverse, including motor impairments, cognitive dysfunctions, vision deficits, depression and fatigue (11–13), causing neurological disability which results in reduction of QoL (14,15). Physical disability and especially motor symptoms in pwMS, are associated with changes in the corticospinal tract (16–21), which is the major neuronal pathway providing voluntary motor function in human (22). Nevertheless, motor symptoms in pwMS can be managed with improvement of neuroplasticity (23–26), which is defined as the ability of the CNS to continuously adapt to changes in the environment (27). Moreover, neuroplasticity has an essential role in clinical condition of pwMS, due to the fact that greater values of neuroplasticity in the stable stage of the disease, can be a strong predictor for a better clinical recovery in the post-relapse stage (28,29). These neuroplastic effects in pwMS, are exerted throughout the propagation of neural signals in the corticospinal system (30), which are associated with the corticospinal tract integrity. To our knowledge, corticospinal plasticity can be probed via Non-Invasive Brain Stimulation techniques, specifically via Transcranial Magnetic Stimulation (TMS) (27). Therefore, corticospinal plasticity can be examined throughout a number of TMS-based neurophysiological measures that exhibit abnormalities in corticospinal excitability, including abnormal motor threshold (MT) and altered central motor conduction time (CMCT) (30).

As far as we know, corticospinal plasticity is exercise-dependent activity (31,32) affected by various factors (33,34), including the different physiotherapeutic approaches (24,35), aerobic exercise (26,36–38) resistance training (26,38) as well as interlimb coordination (39,40). Additionally, several studies (41–44) using healthy participants and chronic stroke survivors (41,42,44,45) reported that bilateral movement instead of unilateral, leads to the greatest increase in corticospinal plasticity due to suppression of the cortical inhibition (45,46) and due to simultaneous activation of homologous representations of the motor cortices (47,48). Still, considering the importance of corticospinal plasticity in the clinical condition of pwMS and due to the fact that cortical lesions can be detected unexpected in both brain hemispheres (49), there is a gap regarding the investigation of the effects of the bilateral movements in corticospinal plasticity and the impact in motor and cognitive functions, in pwMS.

Therefore, the aim of this study is to investigate bilateral corticospinal changes and possible effects in motor and cognitive functions in pwMS, during a 12-weeks different intervention programs based on bilateral versus unilateral movements, adapted to sports activities exercises and fitness functional exercises. Consequently, we assume that possible effects from our study will promote a novel approach in the field of neurorehabilitation and will introduce an innovative type of exercise during the stable stage of the disease.

This research study follows a concurrent multiple baseline design across subjects, which is designed according to the 'What Works Clearinghouse' criteria for single case studies (50). All participants will begin the study with the baseline phase at the same time while the intervention phase is introduced staggered across patients and time. The intervention is introduced systematically in one patient while baseline data collection continues in the others without any intervention. The cause-effect inference can be clearly verified by the staggered duration through separate baseline phases (51). Subsequently, if the intervention (independent variables) will be the only element of improvement in participant's conditions, the proposed outcome measures (dependent variables) will not change for the participants that remain in the baseline phase, but will be improved only for those in the intervention phase. The efficacy of our proposed treatment protocol will be assessed by a single-case experimental design study. Single case methodology refers to the intensive study of one or more participants and recently was ranked as Level 1 evidence for treatment decision purposes (52). Accordingly, it is suggested that properly designed and executed single case studies, have the capacity to demonstrate cause-effect relationships between the independent and the dependent variables, with relatively small sample (50).

The study will take place at the physiotherapy unit of the Cyprus Institute of Neurology and Genetics (CING). All experimenters in the proposed study are health care professionals. All data storage and statistical analysis will take place at the facilities of the Department of Rehabilitation Sciences of Cyprus University of Technology (CUT) and at the physiotherapy unit of the CING. All of the measures are to be administered by the clinical research team member (senior physiotherapist) under the supervision of the project coordinator. All data and personal information collected from the study will be stored safely at the premises of CUT and CING and not shared between researchers. Five years after data collection the measurements will be safely destroyed.

### **Participants and methods**

We will recruit 30 pwMS in total, over the course of five years. The study includes two groups of pwMS, the first one contains 15 people with RRMS and the second one 15 people with SPMS. Each individual from this group will be allocated respectively in another three subgroups of 5 participants according to the type of movement (i.e., subgroup 1: in-phase bilateral sport activities and fitness functional exercises, subgroup 2: anti-phase bilateral sport activities and fitness functional exercises, subgroup 3: unilateral sport activities and fitness functional exercises). Firstly, we will recruit the group of people with RRMS who will participate in the three subgroups with same order as mentioned above. After the first group will finish, we will recruit the group of people with SPMS who will also participate in the three subgroups with same order as mentioned above. The number of participants in each subgroup is justified based on the 'What Works Clearinghouse' criteria for single case studies (50).

Fifteen people with RRMS and Expanded Disability Status Scale (EDSS) (53) score between 3-5 and 15 people with SPMS and EDSS between 3-6 will be

included in the study. All participants will be recruited from the data base of the CING and especially through a referral of the neurologist from the CING, who is the clinical coordinator of the Neuroepidemiological Department and she will evaluate also the EDSS for the needs of this study. The inclusion criteria include 1) people with RRMS with EDSS score between 3–5, 2) people with SPMS with EDSS score between 3-6, 3) aged between 30 and 70 years old, 4) no relapse within 30 days and 5) Mini Mental State of Examination (MMS) score between 24-30 (no cognitive impairment). The exclusion criteria include 1) metal implants, 2) history of any disease affecting the central nervous system other than MS, 3) history of cardiovascular disease, 4) mental disorders, 5) severe orthopedic disorders, 6) pregnancy, 7) visual deficit, 8) hearing impairments, 9) epileptic seizures and 10) spasticity level on upper or lower limbs more than 1+ (slight increase in muscle tone) according to Modified Ashworth Scale (54). Additionally, participants will be advised to continue their usual prescribed medication throughout the study duration and they will be advised to continue their usual routine, avoiding to receive any other exercise program during the study.

All participants will be required to provide consent, after being informed about the process of filing complaints. The experimenter will assign a participant ID number (e.g., Participant 101, 102, etc.). From this point on, the name of each participant will not be used again and only the participant ID number will be used for statistical analyses or other reasons. Subjects, patients and carer/family will be provided with the contact details of the Director of Research and International Relations of the CUT, an independent authority that is unrelated to the study, in the case they wish to make anonymous or branded comments or complaints about this research project. Moreover, subjects will be informed in the consent form that they can be informed about the results of the study relevant to them, following completion of the study. Consent will be perceived by the participants as they are adults without cognitive deficits (see inclusion criteria) and also they have the ability to understand, think, express and write. The participants who will be included in the study will be given a detailed description and explanation of all procedures, analysis of the purpose of the study as well as the benefits and rights that each will have through his/her participation. Finally, all the gathered data will be stored at the principal investigator's office and only the investigators of the study will have access to participants' name and data. Five years after data collection the measurements will be safely destroyed.

The intervention protocols contain bilateral and unilateral movements of the upper limbs which are adapted to exercises based on different sport activities and fitness functional exercises. Regarding the exercises which will be included in the sport activities, the participants will be practiced in basketball, volleyball, boxing and swimming. Due to the fact that no set protocols have been reported regarding the previous mentioned activities, for the needs of this study certified coaches will design adapted protocols related to each sport activity, based on previous literature. Regarding the boxing, an adapted protocol will be designed based on the study of Sangarapillai et al., (55). Concerning the basketball, an adapted protocol related to the basic technical skills will be designed (e.g. different types of dribbling, passing and catching the ball, shooting, relay racing etc). Similarly, an adapted protocol related to the volleyball will be designed based on the basic technical skills (e.g. different types of passing, serving, receiving the ball). Finally, an adapted protocol will also be designed regarding the basic swimming skills from the three main swimming strokes (i.e. crawl, breaststroke, backstroke). On the other hand, the exercises which will be performed regarding the fitness part will be based on a circuit functional training, including exercises with the use of light resistance bands (e.g. towards movement directions of the shoulder, elbow and wrists joints) with the use of their own body weight (e.g.

pushups, TRX) (56). The intervention phase for each participant consists of 12 consecutive weeks in which the proposed protocol will be performed three times per week, for 30-60 minutes each session, in respect of individual levels of fatigue. However, the duration and the intensity of the exercises will be designed considering previous literature (37,57) and recommendations (58). Additionally, for each participant we will perform several neurophysiological and clinical assessments during baseline, intervention and follow up phases. The neurophysiological assessments include evaluation of corticospinal plasticity via TMS (27,30). Corticospinal plasticity characterized via certain TMS-specific neurophysiological measures including resting MT (rMT), motor-evoked potential (MEP) amplitudes and the CMCT (30). Moreover, clinical assessments will be gathered regarding motor skills (i.e., walking, balance, strength, upper limb dexterity) and cognitive functions (i.e., IPS), as well as a subjective questionnaire will be provided to the participants related to fatigue. Age, gender and disease duration since diagnosis will be collected as descriptive measures.

The benefits that all participants will gain are the systematic evaluation of their clinical condition for a long period of time, as well as their participation for a long time in an exercise program which will keep them physically active.

The expected results of this research are:

- 1) Improvement of motor functions (gait, balance, strength, upper extremity functionality).
- 2) Improvement cognitive functions (information processing speed).
- 3) Possibility to increase the plasticity index in both cerebral hemispheres, which means that each patient will have a much better prognosis in a possible relapse, due to the nature of the disease, as well as a qualitative recovery in a such situation.
- 4) Potential reduction of the CMCT in which there will be an improvement in the control of several motor functions, mainly of the upper limbs.
- 5) All participants will also benefit from a number of clinical evaluations and exercise sessions, which are much more in quantity than what they are funded throughout the General Health System.

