### **Study design**

Each subgroup includes five participants and each one constitutes a separate research study that follows a concurrent multiple baseline design across subjects, designed according to the 'What Works Clearinghouse' criteria for single case studies (50). During the experimental procedure, all participants will begin the study with the baseline phase at the same time while the intervention phase is introduced staggered across patients and time (see Figure 1). The intervention will be introduced systematically in one patient while baseline data collection continues in the others without any intervention. The cause-effect inference can be clearly verified by the staggered duration through separate baseline phases (51). Subsequently, if the intervention is the sole cause of improvement in participants' conditions, the proposed outcome measures will not change for the participants that remain in the baseline phase but will be improved only for those in the intervention phase.

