### **Clinical measures analysis**

For each clinical measure (i.e., balance, gait, cognitive function, bilateral hand dexterity and strength) and for the Modified Impact Scale we will calculate the values from each time point across all phases (i.e., baseline, intervention, follow-up) and then we will evaluate the average of them, so to get a single mean value for each measure and for each phase (mean baseline; mean intervention mean follow-up). To investigate the association between the intervention protocol and clinical condition, we will calculate the differences between phases' mean values (i.e., mean baseline; mean intervention; mean follow up), reflecting to the degree of change in clinical condition following in-phase bilateral exercises.

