### **Statistical analysis**

For each of the outcome variables that the visual analysis indicates a potential functional effect, a quantitative analysis will be performed to estimate the effect size. This analysis will be performed for each variable at which a significant trend is shown as described in the previous section. In order to estimate the individual-level effect sizes, we will use three different methods, as suggested by 'What Works Clearinghouse' (50), the standardized mean difference (Cohen's  $d$ ), the standardized mean difference with correction for small sample sizes (Hedges'  $g$ ) and piecewise regression analysis which does not only reflect the immediate intervention effect, but also the intervention effect across time. Multilevel modelling, which is recommended by the 'What Works Clearinghouse' and the single case educational design, specific mean difference index will be used to estimate the magnitude of the effect across cases and compared to the effect obtained by the single level estimates (77). For all the different neurophysiological parameters and clinical conditions, evaluated separately, the null hypothesis is that "there is no improvement from the proposed intervention", thus participants' responses are independent from the condition (baseline versus intervention) under which they were observed. The alternative hypothesis is that "the neurophysiological parameters and /or the clinical condition of the participants will be affected by the specific intervention", again assessed separately. We will reject the null hypothesis if the  $p$  value is smaller than 0.05. All tests will be two sided. Statistical analyses will be performed using the statistical software R (<https://www.r-project.org/>).

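### The aim sets bilateral against unilateral exercise, but no analysis compares the types, and running them in one fixed order in both cohorts aliases type completely with order

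*Protocol*

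**What the plan says.** The title announces "The investigation of the effects of different types of exercise in neuroplasticity and in clinical condition". The aim, at the end of the introduction, is to study corticospinal, motor and cognitive changes "during a 12-weeks different intervention programs based on bilateral versus unilateral movements".

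*Participants and methods*: "We will recruit 30 pwMS in total, over the course of five years". There are two cohorts of 15 (RRMS, then SPMS), each divided by movement type into subgroups of 5: in-phase bilateral, anti-phase bilateral and unilateral. The RRMS cohort goes through the subgroups in the listed order. Once it has finished, the SPMS cohort is recruited, "who will also participate in the three subgroups with same order as mentioned above". No randomisation or counterbalancing of type is mentioned.

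*Study design*, on the subgroups: "each one constitutes a separate research study that follows a concurrent multiple baseline design across subjects".

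*TMS measures analysis* and *Clinical measures analysis* take differences between phase means. The latter describes these as "reflecting to the degree of change in clinical condition following in-phase bilateral exercises".

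*Statistical analysis* sets a null hypothesis under which "responses are independent from the condition (baseline versus intervention) under which they were observed". It names a multilevel model for the size of effect across cases, with no term for exercise type.

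**The concern.** There are two linked problems.

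First, the aim is worded as a comparison and the design builds three types to compare, but every specified analysis is a contrast between phases within participants. If the multilevel model is fitted within a subgroup, it compares no types. If it is fitted over all cases without a type term, it averages them. A reader wanting to know whether bilateral exercise does more than unilateral would be left to set separate results side by side, with no estimate of the difference and no interval.

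Second, in-phase is always first and unilateral always last, in both cohorts. Any comparison of types is then also a comparison of early with late. The second cohort could have broken this link, but repeats it. A statistical analysis plan could add a type term, but it could not separate type from order once the subgroups have been run this way.

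**Working it through.** **1. Sample size.** 2 cohorts × 3 types × 5 participants = 30, which reproduces the stated total. The protocol bases subgroup size on single-case criteria and gives no power, effect size or SD, so there is no power calculation to reproduce.

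**2. Aliasing under the stated order.** Take a participant-level model for the individual effect (intervention minus baseline) with 6 columns: intercept, cohort, two type indicators, two order-position indicators. With the same order in both cohorts, each position column equals a type column. The rank is 4 of 6, so no type contrast can be estimated free of position.

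**3. Other orders for the SPMS cohort** (RRMS stays in-phase, anti-phase, unilateral):

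| SPMS order | Rank of 6 | Type keeping its position |
|---|---|---|
| in-phase, unilateral, anti-phase | 5 | in-phase |
| anti-phase, in-phase, unilateral | 5 | unilateral |
| unilateral, anti-phase, in-phase | 5 | anti-phase |
| unilateral, in-phase, anti-phase | 6 | none |
| anti-phase, unilateral, in-phase | 6 | none |

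Only the two rotations give full rank. Randomising type within each cohort, with types spread over the time positions, also gives 6 of 6.

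**4. Size of a possible bias (illustration).** Number the positions 0, 1, 2 and assume that effect size drifts by 0.1 SD per position. The documents give no such figure.
- Unilateral minus bilateral: 0.1 × [2 − (0 + 1)/2] = 0.15 SD. Drifts of 0.2 and 0.3 SD per position give 0.30 and 0.45 SD.
- Anti-phase minus in-phase: 0.1 × (1 − 0) = 0.10 SD.
- Averaging two cohorts run in the same order leaves both figures unchanged.
- A rotation alone need not remove the bias. With SPMS run as anti-phase, unilateral, in-phase, the mean positions over both cohorts are in-phase (0 + 2)/2 = 1, anti-phase (1 + 0)/2 = 0.5 and unilateral (2 + 1)/2 = 1.5. The bias is then 0.1 × [1.5 − (1 + 0.5)/2] = 0.075 SD unless the model includes position.

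**5. Precision of the missing contrast**, in SD of individual effects, with 30 − 6 = 24 degrees of freedom and t = 2.064:
- Bilateral v unilateral, 20 v 10: 2.064 × √(1/20 + 1/10) = 0.80.
- In-phase v anti-phase, 10 v 10: 2.064 × √(2/10) = 0.92.
- Adjusting for position under a rotation costs precision. Each type sits in 2 of the 3 positions, and each pair of types shares one, so the efficiency is (1 × 3)/(2 × 2) = 3/4. The half-widths become 2.064 × √(0.15/0.75) = 0.92 and 2.064 × √(0.20/0.75) = 1.07.

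**6. Power** for 20 v 10 (noncentral t, two-sided 0.05, before adjustment for cohort or position): 24%, 51% and 70% at assumed differences of 0.5, 0.8 and 1.0 SD. The difference detectable with 80% power is 1.12 SD.

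**The case against.** The strongest reply is that this is a series of single-case studies and not a comparative trial. *Study design* and the null hypothesis say so consistently, the list of expected results contains no difference between types, and no superiority hypothesis is stated. On that reading only the comparative wording of the title and aim is at fault, and rewording cures it. This stands as one acceptable remedy. It does not remove the mismatch, because the aim does set bilateral against unilateral, and the introduction motivates it with studies in which bilateral movement gave the larger gain.

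A second reply is that a phase-by-type term belongs in a statistical analysis plan. That is fair for the model term alone. It does not cover the order, which the protocol itself fixes.

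A reader might also infer four stronger things that the documents do not support:
- **That the study can show nothing.** Each participant is compared with their own baseline, and baselines are concurrent and staggered within each subgroup. The within-type effects, which are what the stated null concerns, are not touched.
- **That equipment drift or calendar shifts bias the type contrast directly.** A slow shift in level moves baseline and intervention together and largely cancels in phase differences. What would bias the contrast is a change in the size of the effect, for example through staff learning or case mix.
- **That in-phase against anti-phase is a stated aim.** It is inferred from the subgroups; the aim sentence names only bilateral and unilateral.
- **That participants are assigned in order of recruitment.** The protocol fixes the order of the subgroups, not how individuals within a cohort of 15 reach them.

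Finally, a 0.15 SD bias is small against a half-width of 0.80 SD. That is true at the assumed drift, but the aliasing does not depend on the drift, and removing it costs little.

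**Conclusion.** The point holds for comparisons between exercise types. The comparison in the aim has no analysis, and the fixed order makes type and order inseparable in both cohorts (rank 4 of 6). *Clinical measures analysis* is wrong on any reading, since it names one type of three.

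The aliasing follows from the stated sequence alone. The size of any bias rests on an assumed drift in effect size: 0.15 SD for unilateral minus bilateral at 0.1 SD per position, 0.45 SD at 0.3. Even with the order repaired, the contrast is imprecise, with a half-width of about 0.80 SD, or about 0.92 SD if position is also adjusted for under a rotation. It can only be exploratory. The order has to be settled before the SPMS cohort starts, because it cannot be repaired in the analysis.

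**What to change.** 1. **Statistical analysis.** Fit the multilevel model over all participants with phase, movement type, cohort and phase by type. Under a rotated order, add phase by cohort and phase by position. Report the bilateral-minus-unilateral difference in effect with a 95% confidence interval, and in-phase minus anti-phase as a further contrast. Label both exploratory.
2. **Participants and methods.** Draw by lot one of the two rotated orders for the SPMS cohort, so that every type changes position. A lot over all orders is not enough, since three of the five different orders stay rank-deficient and one of them keeps unilateral last in both cohorts. Alternatively, randomise movement type within each cohort, with the types spread over the time positions. A lot that only decides who enters which sequential subgroup balances case mix, but not time.
3. **Clinical measures analysis.** Refer to all three types in place of in-phase exercise alone.
4. **If the fixed order is kept.** State that between-type comparisons are non-randomised and confounded with order, or restate the aim as separate within-type evaluations with no claim that one type is superior.

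The cost is one extra model, a changed subgroup order in the second cohort, and a contrast that must be reported as imprecise. Randomising within cohort is harder: types would have to run side by side, and anyone assigned early to a later start might by then fall outside the EDSS range or the 30-day relapse criterion.
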